## Abstract

Chronic pain in Sickle Cell Disease (SCD) is probably related to maladaptive plasticity of brain areas involved in nociceptive processing. Transcranial Direct Current Stimulation (tDCS) and Peripheral Electrical Stimulation (PES) can modulate cortical excitability and help to control chronic pain. Studies have shown that combined use of tDCS and PES has additive effects. However, to date, no study investigated additive effects of these neuromodulatory techniques on chronic pain in patients with SCD. This protocol describes a study aiming to assess whether combined use of tDCS and PES more effectively alleviate pain in patients with SCD compared to single use of each technique. The study consists of a one-session double blind, block-randomized clinical trial (NCT02813629) in which 128 participants with SCD and femoral osteonecrosis will be enrolled. Stepwise procedures will occur on two independent days. On day 1, participants will be screened for eligibility criteria. On day 2, data collection will occur in four stages: sample characterization, baseline assessment, intervention, and post-intervention assessment. These procedures will last ~5 h. Participants will be divided into two groups according to homozygous for S allele (HbSS) (*n* = 64) and heterozygous for S and C alleles (HbSC) (*n* = 64) genotypes. Participants in each group will be randomly assigned, equally, to one of the following interventions: (1) active tDCS + active PES; (2) active tDCS + sham PES; (3) sham tDCS + active PES; and (4) sham tDCS + sham PES. Active tDCS intervention will consist of 20 min 2 mA anodic stimulation over the primary motor cortex contralateral to the most painful hip. Active PES intervention will consist of 30 min sensory electrical stimulation at 100 Hz over the most painful hip. The main study outcome will be pain intensity, measured by a Visual Analogue Scale. In addition, electroencephalographic power density, cortical maps of the *gluteus maximus* muscle elicited by Transcranial Magnetic Stimulation (TMS), serum levels of Brain-derived Neurotrophic Factor (BDNF), and Tumor Necrosis Factor (TNF) will be assessed as secondary outcomes. Data will be analyzed using ANOVA of repeated measures, controlling for confounding variables.

## Introduction

Sickle-cell disease (SCD) refers to the group of hemoglobinopathies in which hemoglobin S plays a relevant role. The most prevalent genotypes are homozygous for S allele (HbSS) and heterozygous for S and C alleles (HbSC). Severity of SCD depends on different genotype, being the HbSS genotype the most severe (Rees et al., 2010). Pain is the major symptom reported by patients with SCD and it is present throughout the life span (Platt et al., 1994). The main cause of pain in SCD is the cyclic presence of ischemic vaso-occlusive events (Ballas, 2015) that can lead to severe bone tissue damage (Ballas et al., 2012), chronic joint pain syndromes (Ejindu et al., 2007) secondary to osteomyelitis, dactylitis, arthritis, and osteonecrosis (Hernigou et al., 2006; Caracas Mda et al., 2013; Flouzat-Lachaniette et al., 2016).

Chronic pain syndromes have a strong impact on quality of life of patients with SCD and lead to significant disability (Ballas, 2005). As seen in many other chronic pain syndromes, radiographic examinations relate poorly with reported pain intensity. Moreover, the effects produced by pain cannot fully explain structural injuries (Duncan et al., 2007; Bedson and Croft, 2008). Non-adaptive changes of brain areas involved in nociceptive information processing, and consequent maintenance of pain over time, may explain the disagreement between pain perception and objective clinical findings (Baliki et al., 2014). This phenomenon is termed as maladaptive plasticity (Kuner and Flor, 2016).

Although the role of maladaptive plasticity in the maintenance of chronic pain in patients with SCD is unsure, several imaging studies (Darbari et al., 2015; Campbell et al., 2016; Case et al., 2017) reveal increased functional connectivity of anterior cingulate cortex, primary and secondary somatosensory cortices (Darbari et al., 2015), as well as the periaqueductal gray matter (Case et al., 2017). These findings appear to relate with high frequency of hospital admissions (Darbari et al., 2015) and enhanced central sensitization (Campbell et al., 2016). Thus, pain in SCD seems to display similar neurobiological characteristics as other chronic pain conditions.

Some biochemical changes may explain chronic pain in SCD. Brain-derived Neurotrophic Factor (BDNF) is involved in neural regulation, maintenance, and synaptic formation, having an important role in the central nervous system plasticity (Park and Poo, 2013). BDNF levels increase in response to inflammatory conditions have been interpreted as an adaptive action related to neural protection (Schulte-Herbruggen et al., 2005; Grimsholm et al., 2008). However, higher levels of BDNF may potentiate NMDA receptors activity in the primary afferent nociceptors terminals (Chen et al., 2014), generating increased sensitization of dorsal horn neurons in response to nociceptive stimuli (Merighi et al., 2008; Biggs et al., 2010). In addition, higher levels of BNDF are associated with greater scores on central sensitization and poorer endogenous inhibitory pain control in individuals with chronic pain (Caumo et al., 2017). Serum levels of BDNF are nearly 130% higher in people with chronic joint pain (Simao et al., 2014) and positively correlated with levels of Tumor Necrosis Factor (TNF) (Grimsholm et al., 2008).

In addition to biochemical changes, electrophysiological variations are reported in brain activity of individuals with chronic pain. A systematic review (Parker et al., 2016) evaluating motor cortex excitability through Transcranial Magnetic Stimulation (TMS) identified a decrease in GABAergic intracortical inhibitory connections at the primary motor cortex (M1). This decrease is inversely correlated with serum BDNF levels (Caumo et al., 2016). Moreover, it appears to potentiate dysfunctional reorganization in M1 (Tsao et al., 2008) due to an overlap (Te et al., 2017), “blurring” (Tsao et al., 2011) and/or decreased somatotopic representation in the region (Schabrun et al., 2015). Chronic pain can be characterized also by abnormal EEG patterns, mainly a preponderance of slow brain rhythms such as delta (Walton et al., 2010), theta, and alpha (Meneses et al., 2016; Pinheiro et al., 2016). Preponderance of slow rhythms might result from significant changes in the thalamocortical loop due to sensitization of structures involved in nociceptive processing (Llinas et al., 1999).

Maladaptive brain plasticity phenomenon may underlie chronic pain and could explain why some individuals display refractory pain not responsive to pharmacological and non-pharmacological analgesic treatments (Barakat et al., 2010; New et al., 2014). Within this context, novel therapeutic strategies are necessary to reverse or diminish the effects of chronic pain. Transcranial Direct Current Stimulation (tDCS) has been investigated in several chronic pain conditions (Andrade et al., 2013; Vaseghi et al., 2014, 2015; Bolognini et al., 2015; Ngernyam et al., 2015) to modify brain maladaptive changes (Antal et al., 2010; Polania et al., 2012; Cioato et al., 2016; Sehyeon et al., 2016). This neuromodulatory technique induces neuroplasticity changes dependent on electrode polarity: anodic stimulation increases corticospinal excitability and cathodic stimulation creates an opposite effect (Nitsche et al., 2008; Nitsche and Paulus, 2011).

Lasting effects of a single tDCS session on human corticospinal excitability depend on stimulation intensity and duration (Nitsche and Paulus, 2000). For instance, healthy subjects that received 13 min of anodic tDCS stimulation over M1 displayed greater corticospinal excitability up to 90 min after the session (Nitsche and Paulus, 2000, 2001). The response to a single tDCS session on serum levels of BDNF in humans, however, remains unclear. Laboratory animal studies showed decrease of serum BDNF levels under experimental pain conditions (Spezia Adachi et al., 2015; Filho et al., 2016), which may happen in human subjects. One tDCS session can also influence EEG brain rhythms (Keeser et al., 2011; Jacobson et al., 2012) and clinical outcomes in humans, including pain (Schabrun et al., 2014). Thus, one-session tDCS protocols may be useful to generate preliminary data to give basis for prolonged use of this neuromodulatory technique.

From the clinical point of view, the effects of tDCS on chronic pain are contradictory (Luedtke et al., 2012, 2015; Wrigley et al., 2013). A recent systematic review (O'Connell et al., 2014) showed that tDCS alone provides little effect on pain control. Thus, more studies are necessary to investigate ways of enhancing its possible therapeutic benefits. Several studies have proposed an association of tDCS with other techniques, such as aerobic exercise (Mendonca et al., 2016), physical therapy (Sakrajai et al., 2014), and Peripheral Electrical Stimulation (PES) (Boggio et al., 2009; Schabrun et al., 2013, 2014; Hazime et al., 2017). These therapeutic associations assume that brain responsiveness to a particular therapy may be facilitated by techniques that alter cortical excitability (Schabrun and Chipchase, 2012). PES is a neuromodulatory technique that can induce transient changes in corticospinal excitability, depending on stimulation intensity, frequency (Chipchase et al., 2011a,b), and duration (McKay et al., 2002). PES with intensity at the sensory threshold decreases excitability, while at the motor threshold has the opposite effect (Chipchase et al., 2011a).

PES and tDCS may have an additive effect, favoring long-term potentiation or long-term depression depending on how they are combined (Muller-Dahlhaus and Ziemann, 2015). When two excitatory stimuli are associated, a null result occurs (Schabrun et al., 2013). Nonetheless, association between inhibitory and excitatory stimuli results in a synergistic effect (Boggio et al., 2009; Hazime et al., 2017). Hence, PES at the sensory threshold associated with anodic tDCS produce a sum of individual analgesic effects. As an example, association of these techniques reduced pain intensity by 36.5% while tDCS alone reduced pain by 15% in individuals with chronic pain (Boggio et al., 2009). The association of the two techniques generated better immediate effects restoring cortical representation of paraspinal muscles (Schabrun et al., 2014) and was more effective in the control of chronic low back pain than their single administration (Hazime et al., 2017).

Currently, pharmacologic interventions are the main treatment for management of chronic pain in subjects with SCD (Yawn et al., 2014). Few clinical trials evaluated the therapeutic potential of non-pharmacologic treatments (Williams and Tanabe, 2016). Consistent data suggest that the association of anodic tDCS and sensory PES is a promising therapeutic strategy for management of chronic pain. To the best of our knowledge, the study described in this protocol is the first investigating the association of these neuromodulation techniques on pain management and neurophysiological aspects of individuals with SCD. Thus, the objectives are: (1) testing the effects of anodic tDCS and PES association on pain control in subjects with SCD HbSS and HbSC genotypes; (2) and measuring the impact of the intervention on neurophysiologic parameters (electroencephalographic power density, TMS cortical mapping of the *gluteus maximus* muscle, and serum levels of BDNF and TNF) in this population.

## Objectives and hypothesis

### Primary objective

Evaluate whether a single session of anodic tDCS associated to sensory PES is superior to reduce pain intensity of individuals with SCD (HbSS and HbSC) compared to individual or sham use of these techniques.

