### Hypothesis

A single session of anodic tDCS associated with sensory PES provides greater analgesic effect compared with single use of the techniques;

The association of anodic tDCS and sensory PES causes greater decrease on serum levels of BDNF and TNF and greater increase on the muscle *gluteus maximus* cortical representation compared to the individual use of the techniques;

A session combining anodic tDCS and sensory PES leads to greater decrease of electroencephalographic low frequency (delta, theta, and alpha) power density compared to the individual use of the techniques in participants with SCD.

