### Sample size

The sample size was calculated using the GPower software version 3.1.9.2 (Faul et al., 2007). The overall study objective is to test the hypothesis that association of anodic tDCS and sensory PES reduces pain intensity by a large percentage as opposed to use of isolated tDCS or PES in individuals with SCD. We assumed that the sample will be equally randomized into four intervention groups: (1) active tDCS + active PES; (2) active tDCS + Sham PES; (3) Sham tDCS + Active PES; and (4) Sham tDCS + Sham PES. We proceeded with the desired sample size assuming no financial or logistic limitations. The parameters used were: 80% power; 5% Type I error; effect size of 0.35 (Cohen, 1977) on the reduction of pain intensity evaluated by the VAS; four intervention groups; two genotypes (HbSS and HbSC) subgroups; and two repeated measures (pre- and post-intervention). Using these parameters yield to an estimated 64 participants for each genotype, a total *n* = 128. To increase the likelihood of achieve the computed sample size in a timely fashion, this clinical trial will be promoted through social media and posters in SCD treatment centers explaining the purpose and potential benefits of the study.

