## Potential pitfalls and counteracting measures

This protocol was designed with the main purpose of answering the question “Does tDCS combined with PES have an additive effect in the control of osteonecrosis joint pain associated with SCD?” As in any clinical trial, risk of bias and errors exist. Several strategies will be used to reduce them:

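### The primary objective admits sham as an alternative comparator while the abstract, hypothesis and sample-size text do not, so a win over sham or over one inert technique could be reported as superiority of the combination

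*Protocol article*

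**What the plan says.** The protocol article describes the comparator of the combination in five places:

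- Abstract: the study assesses whether the combination will "more effectively alleviate pain in patients with SCD compared to single use of each technique". Sham is not named.
- Primary objective: the question is whether the combination is "superior to reduce pain intensity of individuals with SCD (HbSS and HbSC) compared to individual or sham use of these techniques". This is the only statement that brings in sham, and it does so with *or*.
- Hypothesis: the combination "provides greater analgesic effect compared with single use of the techniques". Sham is not named.
- Sample size: the combination "reduces pain intensity by a large percentage as opposed to use of isolated tDCS or PES in individuals with SCD". Sham is not named; the two techniques are joined by *or*.
- Potential pitfalls and counteracting measures: the main question is "Does tDCS combined with PES have an additive effect in the control of osteonecrosis joint pain associated with SCD".

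The Statistical analysis section specifies a repeated-measures ANOVA with intervention group (four levels), genotype and time, with Bonferroni correction and a 5% level. It does not say which group comparisons the correction covers or which of them decides the primary claim.

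**The concern.** The trial exists to learn whether adding one technique to the other helps. Only the comparisons with the two single-technique arms bear on that. A win over double sham shows that something in the combination works. A win over one single technique shows that the other component contributes. Neither shows that both components are needed.

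The primary objective is the sentence against which a positive result will be reported, and it is the one that admits sham. A later analysis plan could adopt either reading and cite the protocol for it. Under the loose reading, the report could claim superiority for a combination no better than one of its parts, which would answer neither the Hypothesis section nor the stated main question. Bonferroni gives no protection: the win over sham or over the inert technique is a true difference. It simply answers another question.

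**Working it through.** **Stated sample size.** The inputs in the Sample size section are power 80%, type I error 5%, effect size 0.35, four interventions, two genotypes, two measurements and N = 128. I take 0.35 as Cohen's f (assumption). For a one-way omnibus F test over 4 × 2 = 8 cells, λ = f²N = 0.35² × 128 = 15.68 on 7 and 120 df, which gives power 0.814. The smallest N reaching 80% is 125, or 128 in equal cells. So 128 is reproduced, but by an omnibus test. A four-group between-subject test giving 64 per genotype also fits if the pre-post correlation, which is not stated, is near 0.30. Neither sizes a comparison of the combination with a single technique.

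**What a win means under each reading.** Per intervention there are 2 × 16 = 32 participants with genotypes pooled. Assumptions: normal change scores with SD 1, pooled variance, no dropout and no covariate gain. In the scenario, one technique works by d SD, the other is inert, and the combination equals the working one. It is plausible on the protocol's own Introduction, which cites a systematic review finding little effect of tDCS alone on pain.

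Each pairwise t test has noncentrality d / √(2/32) = 4d, that is 2.0, 2.8 and 3.2 for d = 0.5, 0.7 and 0.8. Bonferroni uses 0.05/6 for all 4 × 3 / 2 = 6 pairs, or 0.05/3 for the combination against the other three arms. Probabilities that the combination wins (simulation, 200,000 trials):

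| d | Beats sham, six pairs | Beats at least one arm, six pairs | Beats at least one arm, three comparisons | Same, and omnibus F significant | Beats both single techniques, each at 5% |
|---|---|---|---|---|---|
| 0.5 | 0.254 | 0.383 | 0.490 | 0.464 | 0.023 |
| 0.7 | 0.548 | 0.710 | 0.797 | 0.790 | 0.025 |
| 0.8 | 0.697 | 0.839 | 0.898 | 0.896 | 0.024 |

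The last column is bounded by 0.025 because the combination truly equals one technique and can beat it falsely, in the favourable direction, only 2.5% of the time. With all four arms equal, the at-least-one rule with Bonferroni over three gives 0.023 in the combination's favour.

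**Power of the both-techniques rule.** Spread f = 0.35 on the change score over the four arm means, in the order combination, tDCS, PES, sham:

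- Only the combination works (1, 0, 0, 0): the SD of the means is d√3/4, so d = 0.35 × 4/√3 = 0.81 against each single technique.
- Published pattern (36.5, 15, 15, 0): 36.5% and 15% are from the Introduction; PES equal to tDCS and sham at zero are assumptions. The SD of the means is 13.0, so d = 0.35 × 21.5/13.0 = 0.58.
- Additive (2, 1, 1, 0): the SD of the means is 0.707, so d = 0.35/0.707 = 0.495.

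| Pattern | Both wins, each at 5%, N = 128 | Both wins, Bonferroni over six pairs | Total N for 80%, each at 5% |
|---|---|---|---|
| Only the combination works | 0.82 | 0.57 | 124 |
| 36.5 / 15 / 15 / 0 | 0.48 | 0.21 | 236 |
| Additive | 0.34 | 0.12 | 324 |

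**The case against.** The best defence is that nothing here is a decision rule. These are an aim, an objective, a hypothesis and a lead-in to a sample-size calculation, and the decisive contrasts may be fixed in an analysis plan that is not shown. Three of the statements name the same two comparators. In ordinary usage, superior to A or B often means superior to both, which would make the primary objective the strictest statement. The hypothesis and the main question already show the intended target.

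Much of this stands. A reader might infer that the protocol sets out several competing success rules, or that it declares success on a win over sham. The text supports neither: no success rule is written, and the real textual difference is sham in the primary objective together with an ambiguous *or*. A reader might also infer an inflated false-positive rate. It is not: with all arms equal, the at-least-one rule with Bonferroni over three stays near 2% in the combination's favour.

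What does not fall away is that the governing sentence is looser than the hypothesis it should match, and the analysis section does not resolve the difference. Leaving detail to an analysis plan does not repair a protocol whose own statements of the target disagree.

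**Conclusion.** The point holds in a limited form. The primary objective and the hypothesis do not name the same comparators, and the literal wording of the objective would let a result that does not answer the hypothesis support a superiority claim.

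If that reading were used and the combination merely equalled one active technique, a supporting win would occur in about 38% to 84% of trials with Bonferroni over six pairs, or 49% to 90% over three, against at most 2.5% when both single techniques must be beaten. These figures rest on 32 per arm and an assumed effect of 0.5 to 0.8 SD, because the protocol gives no SD for the VAS change. They show how often the loose reading would be satisfied, not that the investigators would use it. The stated 128 is not an arithmetic error; it fits an omnibus test.

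**What to change.** Use one wording in the abstract, primary objective, hypothesis and sample-size section: the combination is declared superior only if it beats active tDCS + sham PES **and** sham tDCS + active PES on the VAS. Amend the Statistical analysis section to match: each of these two tests at two-sided 5%, with no Bonferroni split between them because both must succeed. Label combination versus double sham as supportive and unable to carry the primary conclusion on its own.

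The text change is small. The cost is a stricter criterion than the *or sham* reading and, under two of the three patterns above, power well below 80% at N = 128. The sample-size section should therefore describe its 80% as applying to the omnibus test, not to this claim. Against that, the two unsplit tests give more power for the hypothesis as written than Bonferroni over six pairs (0.82 against 0.57, 0.48 against 0.21, 0.34 against 0.12).

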### Secondary objective

Evaluate the effect of a single session of anodic tDCS associated with sensory PES on the following neurophysiological variables: electroencephalographic power density, TMS cortical mapping of the *gluteus maximus* muscle, and serum levels of BDNF and TNF;Evaluate whether therapeutic response varies according to genotypes HbSS and HbSC.

### Hypothesis

A single session of anodic tDCS associated with sensory PES provides greater analgesic effect compared with single use of the techniques;

The association of anodic tDCS and sensory PES causes greater decrease on serum levels of BDNF and TNF and greater increase on the muscle *gluteus maximus* cortical representation compared to the individual use of the techniques;

A session combining anodic tDCS and sensory PES leads to greater decrease of electroencephalographic low frequency (delta, theta, and alpha) power density compared to the individual use of the techniques in participants with SCD.

## Methodology

### Study design, description of allocation, and blinding

This is a clinical, parallel, controlled, block-randomized, double blind trial. The study will occur in 2 days at the Clinical Electrophysiology Laboratory of the Federal University of Bahia, Brazil. An assistant researcher not involved in any other stage of the study will generate an allocation sheet (www.randomization.com) creating four groups for each SCD genotype (HbSS and HbSC), totaling eight experimental groups. Allocation concealment will be enforced using sealed opaque envelopes listed in ascending order, and the allocation secrecy will be maintained until the end of the analyses. The allocation envelope will be opened on the day of the intervention according to the order of inclusion of the study participant. The envelope will contain one of the following interventions: (1) active tDCS + active PES (*n* = 16); (2) active tDCS + sham PES (*n* = 16); (3) sham tDCS + active PES (*n* = 16); (4) sham tDCS + sham PES (*n* = 16) (Figure 1). These interventions will be tested either in the HbSS (*n* = 64), and HbSC (*n* = 64) groups, totalizing 128 participants.

